| Clinical (Wt, TB & OI status)                   | Clinician's notes       | Clinicians/nurses/adherence counsellors          | Every visit                                       |
| Immunological (CD4)
Virological (viral load) | Laboratory records      | Laboratory scientists                            | Baseline & 6mths                                  |
| Medication adherence                            | Adherence questionnaire | Research assistants/nurses/adherence counsellors | Baseline, then every visit (particularly 3&6mths) |

- **Data Storage:** All data generated from this study will be stored for a maximum of 3 years after the completion of the study, after which they will be destroyed. However, during this period they will remain joint intellectual property of Universiti Putra Malaysia and Hospital Sungai Buloh.

**Primary Outcomes:** The first primary outcome is (improved) patient adherence to ART at six months. This is assessed by self-report using a standardized questionnaire of the number of pills missed in the last 30 days and calculating percent adherence based on the expected number of doses taken and/or number of missed doses. Percent adherence will be analyzed as continuous variable and polytomous variable. Subjects will be considered as "Good adherence" when they achieve an optimal adherence cut of >95% of medications taken as directed with <3 missed doses in the last 30 days period. "Fair adherence" will be considered as 80-95% of medications taken as directed with 3-8 missed doses in the last 30 days period, while "Poor adherence" will be considered as <80% of medications taken as directed with >8 missed doses in the last 30 days period. Medication adherence will be assessed at each follow-up visit, particularly at months 3 and 6. The six month scheduled follow-up is the primary analysis but the three month assessment will allow for evaluating trends but is not the primary outcome.

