The second primary outcome is (regularity of) scheduled clinic attendance at six months. This will be assessed from records of scheduled clinic visits in the medical records unit and supported by record of scheduled drug pick-up in the pharmacy. Regularity of scheduled clinic visits will be calculated based on number of scheduled clinic visits attended and/or number of times defaulted. Number of missed appointments will be analyzed as a continuous variable and polytomous variable. Subjects will be considered as "Regular clinic attendee" if they never missed any scheduled clinic appointment. A "Defaulter" will be a patient who has missed one or more scheduled clinic appointment for any reason(s), while a patient will be considered "Lost-to-follow-up" if s/he refuses to show up for scheduled clinic visit for 3 consecutive months, after 3 consecutive attempts to track the client and bring them back on treatment. The six month scheduled follow-up is the primary analysis but the three month assessment will allow for evaluating trends.

**Secondary Outcomes:** The first secondary outcome is (improved) clinical status of patients at six months. This will be assessed by measuring their weights, assessing their TB and opportunistic infection status at every clinic visits, particularly at three and six months and comparing these with the baseline status. Patients' weight is routinely measured and recorded by nurses at the study site, as part of standard patient management protocol. These records will be accessed and utilized in the analysis. Patients' TB status is also routinely assessed and recorded by clinicians/nurses/adherence counselors at every clinic visits. These records will be accessed and utilized to categorize patients into four groups, namely "No signs and symptoms of TB", "TB suspected and referred for evaluation", "Currently on INH prophylaxis" and "Currently on TB treatment". Opportunistic infection status will be assessed through WHO clinical staging at every clinic visits. The six month scheduled follow-up is the primary analysis but trend will be evaluated at three months.

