The other secondary outcome is (improved) immunologic status/response of patients at six months. This will be assessed based on records of two (2) laboratory measurements – CD4 T cell count and viral load. Patients' CD4 count results at six months will be assessed and compared with baseline values to determine if there's a consistent increase (or otherwise) as expected with strict medication adherence. If patients are adherent to ART regimens, absorb the drugs normally, and if their virus is not resistant to the ART drugs in the regimen, it is expected that their CD4 count should increase from baseline levels by at least 50 cells per microliter of blood within 6-12 months of initiating treatment. CD4 count value at six month scheduled follow-up is the primary analysis.

Similarly, plasma HIV RNA load results at six months will be assessed and compared with baseline levels to determine if there is a significant suppression at six months. If patients are adherent to ART regimens, absorb the drugs normally, and if their virus is not resistant to the ART drugs in the regimen, it is expected that their plasma HIV load should be suppressed to undetectable levels (<400 copies/ml) by six months and remain suppressed thereafter. Analysis of "suppressed" (<400 copies/ml) versus "failure to suppress" (>400 copies/ml) at six months as a dichotomous variable is the primary analysis.

**Data analysis:** Data collected will be collated, checked, cleaned, entered into and analyzed using Statistical Package for Social Sciences software (SPSS) version 21 and AMOS software. Parametric tests (T-test, repeated measures ANOVA) and non-parametric tests will be conducted on the data. P value for test of significance of results will be set at 0.05, alpha level (Type 1 error) at 0.05 (Confidence Interval of 95%), Power at 80% to detect an impact of 15% in the fraction of patients with adherence of at least 90% (assuming a no intervention median adherence level of 90%) using a two-tailed test, Z=1.96, and strength by effect size analysis. Analysis will be by intention-to-treat and complete case analysis.

| Independent variable                                                    | Dependent variable                                                           | Type of analysis                                                           |

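### Two primary outcomes, each analysed in two unranked forms at a single 0.05 level, leave the false-positive rate for a primary claim above 5% unless a decisive form and a success rule are fixed

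*Protocol*

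**What the plan says.** All of the following is in the Protocol, section B, Research methodology.

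- **Two primary outcomes.** "The first primary outcome is (improved) patient adherence to ART at six months", and "The second primary outcome is (regularity of) scheduled clinic attendance at six months".
- **Two forms of each.** For adherence: "Percent adherence will be analyzed as continuous variable and polytomous variable", the categories being good, fair and poor. For attendance: "Number of missed appointments will be analyzed as a continuous variable and polytomous variable", the categories being regular attendee, defaulter and lost to follow-up. Neither form is ranked above the other.
- **One time point.** Month 6 is primary. Under the first primary outcome the text reads "The six month scheduled follow-up is the primary analysis but the three month assessment will allow for evaluating trends but is not the primary outcome".
- **One level.** Under Data analysis: "P value for test of significance of results will be set at 0.05, alpha level (Type 1 error) at 0.05", two-tailed with Z = 1.96.
- **The success rule.** H2 (Research hypotheses) speaks of treatment adherence and clinical outcomes together. The first of the expected outcomes explains treatment adherence as medication adherence plus regular attendance. Neither place states a decision rule.

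**The concern.** The protocol settles when the primary comparison is made but not what it is. Each primary outcome has two versions of equal standing, both read at 0.05, and two outcomes make four primary comparisons. The Data analysis section calls that 0.05 the Type 1 error. Without a rule linking the four comparisons, 0.05 is the error of each one and not of the conclusion that reminders improve adherence or attendance.

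The protocol does name a decisive form elsewhere. For viral load, a secondary outcome, it makes suppressed versus not suppressed the primary analysis. The power statement does not fill the gap for adherence: it uses the fraction with at least 90% adherence, a cut-point that matches none of the three adherence categories (above 95%, 80–95%, below 80%).

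At stake is whether a positive report can be taken at its stated level. A reader shown one significant version out of four could not tell whether it was the one intended.

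**Working it through.** **The plan's own figure.** The stated alpha is used in the sample-size calculation, with SD 132, difference 50 and 80% power. With the difference squared in the denominator, n = 2 × 132² × (1.96 + 0.842)² / 50² = 109.4, so 110 per group, as stated. (The square is missing from the printed expression.) This calculation is for one CD4 comparison at 0.05. CD4 is a secondary outcome, and no multiplicity enters.

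**Count of primary comparisons.** 2 outcomes × 2 forms × 1 time point = 4. Month 3 is not counted.

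**Independent tests.** P(at least one false positive) = 1 − 0.95^k.
- k = 2: 1 − 0.9025 = 9.75%.
- k = 4: 1 − 0.8145 = 18.5%. Two codings of one variable cannot be independent, so this is an upper bound.

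**Correlated tests.** The documents give no correlations, so these are assumed. Take four standard normal test statistics with correlation w between the two forms of an outcome and b between outcomes. Count how often any |Z| exceeds 1.96 when nothing works (1,000,000 draws per cell).

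| w | b = 0 | b = 0.3 | b = 0.5 |
|---|---|---|---|
| 0.5 | 17.3% | 16.7% | 15.6% |
| 0.8 | 15.1% | 14.5% | 13.8% |
| 0.9 | 13.5% | 13.2% | 12.4% |
| 0.95 | 12.5% | 12.2% | 11.6% |

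From the same runs:
- Two outcomes, one fixed form each: 9.0–9.8%.
- One outcome, either form may be claimed: 9.1% at w = 0.5, 7.8% at w = 0.8, 7.0% at w = 0.9, 6.4–6.5% at w = 0.95.
- Both outcomes required, each by either form: 0.4–2.6% when neither outcome responds. When one outcome responds strongly, the joint claim rests on the other, and the error approaches that outcome's own 6–9%.

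**Cross-check with actual tests.** A null simulation used 110 per arm and a t-test plus a three-category chi-square test for each outcome. It was run 3,000 times at each between-outcome correlation of 0, 0.3, 0.5 and 0.8, with assumed distributions for missed doses and visits. It gave 8.1–8.7% for one outcome in two forms, 9.2–10.1% for two outcomes by t-test only, and 13.4–15.1% for all four comparisons.

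**Power cost of splitting alpha.** A test with 80% power at 0.05 has power Φ(1.960 + 0.842 − 2.241) = Φ(0.56) = 71% at 0.025. That starting point of 80% belongs to CD4. For adherence, read the power statement as 50% versus 65% reaching at least 90% adherence. This is an assumption: a control median of 90% puts half the patients at or above it, and the 15% impact is taken as percentage points. With 121 per arm and pooled proportion 0.575:
- At 0.05: (0.15 × √121 − 1.960 × √(2 × 0.575 × 0.425)) / √(0.25 + 0.2275) = (1.650 − 1.370) / 0.691 = 0.405, power 66%.
- At 0.025: (1.650 − 1.567) / 0.691 = 0.120, power 55%.

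**The case against.** **This belongs in the statistical analysis plan.** Ranking forms and splitting alpha are often left to that document, which is not shown. That would answer a complaint of silence. But the protocol itself gives both forms equal standing and sets the single 0.05, so a later plan would have to change the protocol's rule and not merely complete it.

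**The wording leans towards requiring both outcomes.** H2, H3 and the first expected outcome each speak of adherence and attendance, or adherence and clinical results, jointly. Nowhere does the protocol say that any one significant test is success. This stands, and it means the 11.5–17% range applies only under an either-outcome reading. Even so, joint wording is not a decision rule, and the choice of form inflates the error under the both-outcomes reading too.

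**No family-wise control was promised.** This also stands in part. The 0.05 sits in one sentence with the power, the Z value and the effect, and is not described as trial-wide. The point is that the label Type 1 error fits a single comparison, while the primary claim has four.

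**The analysis table narrows the form.** It names adherence as a dependent variable only as a categorical level. But it does not name clinic attendance at all, and it does not withdraw the continuous analysis of either primary outcome.

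**A stronger reading to avoid.** A reader might infer from "Parametric tests (T-test, repeated measures ANOVA) and non-parametric tests will be conducted on the data" that each primary outcome is tested by both types of test, making eight primary tests. The sentence concerns the data in general. The table attaches t-test and repeated measures ANOVA to weight, CD4 and viral load, and logistic regression to adherence level. Nothing assigns both types to one primary variable, so the count stays at four.

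**Conclusion.** The point holds in a limited form. Two primary outcomes, two unranked forms of each and one 0.05 level are written into the protocol, and no explicit success rule joins them. The size depends on the reading:

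- any one of four comparisons suffices: about 11.5–17%, with 18.5% as the independence bound;
- either outcome suffices, one form each: 9–10%;
- both outcomes required, form left open: about 6–9% for each outcome.

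These figures assume within-outcome correlations of 0.5–0.95 and between-outcome correlations of 0–0.5, none of which the documents supply. A reader might take a single figure such as 14.5% (w = 0.8, b = 0.3) or 18.5% as the trial's error rate. The documents support only a range that depends on the reading.

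**What to change.** Before results are seen, amend the primary-outcome and data-analysis text as follows.

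1. Name one decisive form and one test for each primary outcome at month 6, for example percent adherence, and all scheduled visits attended yes or no. Label every other form supportive.
2. State the success rule. Either test the two outcomes with Holm at an overall two-sided 0.05, or state that H2 is claimed only if both are significant at 0.05.

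This needs wording only, with no new data. The cost is power. A straight split to 0.025 takes an 80% test to about 71%. For the adherence effect read as 50% versus 65%, 121 per arm gives about 66% at 0.05 and 55% at 0.025. Holm loses less, because the second outcome is tested at 0.05 once the first passes at 0.025. The both-required rule needs no split, but its joint power cannot exceed that of the weaker outcome. As the worked sample size is for CD4, power for the two chosen primary forms should be stated when they are fixed.

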The baseline questionnaire shall consist of sections A – I (A: Patient's readiness and understanding of treatment plan, B: Patient's social support and disclosure status, C: Possible reasons for missing medications, D: Assessment of time and duration of missed doses, E: Assessment of psychosocial stress/difficulties in the past one week, F: Assessment of psychosocial stress/difficulties in the past one month, G: Assessment of alcohol and drug use profile (past & current, degree of usage), H: Patient's background (socioeconomic characteristics, sexual orientation and behaviour) and I: Symptom review of the past 4 weeks). Responses to questions A-C, E will be graded on a 4-point scale, question D, F & I on a 5-point scale, G on a 6-point scale, H will have 7 questions on socioeconomic and demographic characteristics.

The follow questionnaire shall consist of sections A – H (A: Review of current medication and number of missed doses and days of missed doses, B: Number of doses missed in the past 4 days, C: How closely the patient followed dosing schedule, D: Review of any dietary specifications with the drugs, E: Whether the patient missed medications on weekends, F: When was the last time the patient missed medications, G: Possible reasons for missing medications, H: Symptom review of the past 4 weeks). Responses to questions C, D, F & H are graded on a 5-point scale, E on a 2-point scale, and G on a 4-point scale.

| Type of information                             | Source                  | Responsible person                               | Time of collection                                |
|-------------------------------------------------|-------------------------|--------------------------------------------------|---------------------------------------------------|
| Socio-demographic                               | Medical records         | Medical records officer                          | At enrolment                                      |
| Clinic visits                                   | Medical records         | Medical records officer                          | Every visit                                       |
| Medication refill                               | Pharmacy records        | Pharmacists                                      | Every visit                                       |

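### The Good, Fair and Poor adherence categories of the first primary outcome pair percent bands with 30-day missed-dose counts that conflict at every whole number of daily doses

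*Protocol*

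**What the plan says.** Protocol, section B (Research methodology), Primary Outcomes, sets three categories for self-reported adherence at six months:

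- Good: ">95% of medications taken as directed with <3 missed doses in the last 30 days period".
- Fair: "80-95% of medications taken as directed with 3-8 missed doses in the last 30 days period".
- Poor: "<80% of medications taken as directed with >8 missed doses in the last 30 days period".

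The same paragraph takes its raw input as the "number of pills missed in the last 30 days" and describes "calculating percent adherence based on the expected number of doses taken and/or number of missed doses". Percent adherence is to be analysed both as a continuous and as a polytomous variable. The number of doses expected per day is not given, and no rule says which criterion prevails when percent and count disagree.

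The table under Data analysis lists adherence level among the categorical dependent variables, for multivariate/multinomial logistic regression. A further row converts all dependent variables to categories for structural equation modelling and chi-square tests. The continuous dependent variables that the table names are weight, CD4 count and viral load.

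**The concern.** A fixed number of missed doses is a different percentage under each dosing frequency, so a count band can match a percent band only for a particular number of expected doses. If no realistic number satisfies all three pairs, the rule cannot place every patient in exactly one category.

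At stake is the categorical form of the first primary outcome. The 95% cut is also the level that the protocol's Background and Literature Review give as the minimum for treatment success, so whether a patient is Good or Fair carries clinical meaning in this study.

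**Working it through.** **Inputs.** The bands come from Primary Outcomes: Good >95% and <3 missed, Fair 80-95% and 3-8 missed, Poor <80% and >8 missed, all over 30 days. The expected number of doses, N, is not in the protocol. It is assumed here as a range: N = 30, 60, 90 and 120, for one to four doses a day. This is not a statement about which regimens the patients take.

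**Formula.** Percent adherence = 100 x (N - m)/N, with m missed doses. Each m from 0 to N is classified once by percent and once by count.

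**Each scale alone.** >95 / 80-95 / <80 has no gaps or overlaps, and neither does <3 / 3-8 / >8. The fault lies only in pairing them.

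**Once daily, N = 30.**
- m = 2: 28/30 = 93.3%. Good by count, Fair by percent.
- m = 6: 24/30 = 80.0%. Fair on both.
- m = 7: 23/30 = 76.7%; m = 8: 22/30 = 73.3%. Fair by count, Poor by percent.

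**Twice daily, N = 60.**
- m = 2: 58/60 = 96.7%, Good on both. m = 3: 57/60 = 95.0%, Fair on both. The Good/Fair boundary is consistent.
- m = 9, 10, 11, 12: 85.0%, 83.3%, 81.7%, 80.0%. Poor by count, Fair by percent.
- m = 13: 47/60 = 78.3%. Poor on both.

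**Summary over the assumed range.**

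| Doses in 30 days | Missed counts in conflict | Number of counts | Counts that match the percent bands (Good / Fair / Poor) |
|---|---|---|---|
| 30 | 2, 7, 8 | 3 | 0-1 / 2-6 / 7 or more |
| 60 | 9-12 | 4 | 0-2 / 3-12 / 13 or more |
| 90 | 3-4, 9-18 | 2 + 10 = 12 | 0-4 / 5-18 / 19 or more |
| 120 | 3-5, 9-24 | 3 + 16 = 19 | 0-5 / 6-24 / 25 or more |

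**Is there any N at which the pairs agree?** Four conditions must hold together:
- 2 missed must exceed 95%: 2/N < 0.05, so N > 40.
- 3 missed must be at most 95%: 3/N >= 0.05, so N <= 60.
- 8 missed must be at least 80%: 8/N <= 0.20, so N >= 40.
- 9 missed must be below 80%: 9/N > 0.20, so N < 45.

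Together these give N = 41 to 44 doses in 30 days, about 1.4 a day. No whole number of daily doses gives that, so supplying the regimen would not rescue the definition.

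**The case against.** The strongest reply is that percent is meant to govern. The protocol says that percent adherence is the variable to be analysed in polytomous form, so the counts could be a loose gloss, and percent alone classifies everyone. This shows which scale to keep. It does not settle the text as written, which joins the two criteria and subordinates neither. A statistical analysis plan, not shown here, could add a precedence rule, but it would then be overriding a stated definition rather than filling a gap.

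Three limits stand. The continuous analysis of percent adherence is untouched. At twice daily the Good/Fair boundary is sound, so a patient with two missed doses changes category only under once-daily dosing. The check counts possible values of missed doses, not patients; nothing in the protocol gives the share of patients affected.

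A reader might also infer more than the protocol supports:

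- *That and/or lets the rater choose between percent and count.* It joins two inputs to the percent calculation, not the two sets of bands.
- *That only a four-day recall is collected, so one missed once-daily dose already means 75% and Poor.* Follow-up section B is "B: Number of doses missed in the past 4 days", but section A also counts missed doses, with no window stated, and Primary Outcomes refers to 30 days. The protocol nowhere proposes a percentage over four days.
- *That the ambiguity would bias the comparison, through an unblinded choice of rule or a different regimen mix by arm.* The protocol states that investigators are blinded and does not say that anyone picks the rule knowing the arm. Allocation is randomised 1:1 and the intervention does not assign drugs, so regimen imbalance could arise only by chance. Neither route is shown.

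**Conclusion.** The category definition is wrong as written. For one to four doses a day, some counts of missed doses satisfy the percent band of one category and the count band of another: 3 counts at once daily, 4 at twice daily, 12 at three times and 19 at four times daily. Patients with those counts belong to no category if both criteria are required, and to two if either is enough. The tabulated analyses that use adherence level as a category inherit the problem; the continuous analysis does not.

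The size for any given regimen rests on the assumed doses per day. That a conflict exists does not, because agreement needs 41 to 44 doses in 30 days. The effect on the treatment comparison is not known, and no direction of bias is claimed.

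**What to change.** Define the category by percent alone: 100 x (prescribed doses - missed doses)/prescribed doses over the last 30 days, with the protocol's own cut-offs of Good >95%, Fair 80-95% and Poor <80%. Every patient then falls in exactly one category under any dosing frequency.

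Delete the missed-dose counts from the three definitions, and write doses where the outcome paragraph now says pills. Confirm that the missed-dose item in section A of the follow-up questionnaire covers 30 days and that the prescribed number of doses is recorded with it; if not, add the item.

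The cost is one corrected paragraph and at most one questionnaire item, with no extra visits or patients. The stated sample size is based on CD4 count and does not change.

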## RESEARCH APPROACH

### B. Research methodology

**Study Location:** The study will be conducted in Hospital Sungai Buloh, Selangor, Malaysia.

**Study Design:** It will be an experimental (randomized Controlled Trial) study design, single-blinded among newly diagnosed HIV positive patients who are eligible to commence ART from December 2013 to August 2014. Following enrollment and allocation to study arm, baseline adherence, clinical symptoms, CD4 count, viral load, Weight, TB status and Opportunistic infection index will be assessed and measured for the 2 groups, prior to the commencement of ART. The intervention group will receive appointment and medication reminders by text-messaging and telephone calls, in addition to standard care. Based on the Theory of Planned Behaviour Model (Ajzen, 1985), appointment reminders will be sent by Short Text Message (in Malay and English languages) three days prior to each individual client's scheduled appointment and telephone call reminders a day prior to the scheduled clinic appointment visits. Weekly short text messages will also be sent to clients to remind them of taking their medications. The control group will only receive standard care and paper-based appointment during clinic visits. Both groups of clients will be followed up for a period of 6 months on ART. Repeated CD4 count, viral load, Weight, TB status and OI index assessment and measurements will be conducted at 3 and 6 months, respectively to determine treatment outcome. Medication adherence will be measured using structured self-report questionnaires. Clinic visits will be measured through medical records of clinic attendance and clinicians' notes.

**Study Duration:** Recruitment and data collection will be from December 2013 to February 2015.

**Study population:** The study population is all HIV positive clients assessed and found to be eligible for ART commencement at Hospital Sungai Buloh, Selangor

**Inclusion criteria:** Age range of 15 to 65 years eligible to commence ART, able to read text messages and have a mobile phone access.

**Exclusion criteria:** Clients who are previously or currently on ART, foreigners & pregnant patients

**Sampling frame:** It is the list of all HIV positive clients assessed and found to be eligible for ART from December 2013 to August 2014 in Hospital Sungai Buloh, Selangor

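### The second primary outcome's raw count of missed appointments has no denominator, no fixed set of visits and no rule for visits after drop-out, so the arm difference depends on booking practice

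*Protocol*

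**What the plan says.** Under Primary Outcomes, the protocol bases attendance on two undivided counts: "Regularity of scheduled clinic visits will be calculated based on number of scheduled clinic visits attended and/or number of times defaulted". It then names the analysed variable: "Number of missed appointments will be analyzed as a continuous variable and polytomous variable". Three labels follow. A Regular clinic attendee has no missed appointment, a Defaulter has at least one for whatever reason, and a patient is Lost-to-follow-up "if s/he refuses to show up for scheduled clinic visit for 3 consecutive months", after attempts at tracking.

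The number of scheduled visits per patient is not stated. Study Design says "Both groups of clients will be followed up for a period of 6 months on ART" and places repeat assessments at 3 and 6 months. Intervention Protocol names months 1, 3 and 6, but only as the minimum for counselling sessions in the intervention arm. On how appointments are made, Study Design says "The control group will only receive standard care and paper-based appointment during clinic visits".

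The first primary outcome, by contrast, is scaled to what was expected, by "calculating percent adherence based on the expected number of doses taken and/or number of missed doses".

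**The concern.** A count of misses is comparable between patients only if they had the same number of appointments to miss. Here that number may depend on whether the patient stays in care. If a new appointment is issued only when the patient attends, someone who disappears early has little left to miss, while someone who stays keeps being booked and can add further misses.

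Retention is one of the things the reminders are meant to improve. A count whose exposure depends on retention therefore mixes the treatment effect with the opportunity to be counted. The plan also calls for an intention-to-treat analysis, so patients who drop out must be given a value, and the plan does not say how to obtain it. At stake is the size, and possibly the direction, of the between-arm difference on a primary outcome.

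**Working it through.** The plan gives no expected figure for attendance, so there is none to reproduce. Its sample size rests on CD4 count and plays no part here. The one relevant input is the 10% attrition allowance under Sample size (110 + 11 = 121 per group). All rates below are assumptions.

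**Illustration 1: drop-out at each visit.** There are K planned visits. At each visit a patient still in care drops out with probability d (that visit is missed) or otherwise misses sporadically with probability p.

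- As booked, counting stops after the visit at which the patient disappears. Mean misses = [d + (1−d)p] × Σ(1−d)^k, for k = 0 to K−1.
- On a fixed schedule, all K visits count. Mean misses = K − (1−p) × Σ(1−d)^k, for k = 1 to K.

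With K = 3, p = 0.10, d = 0.08 (control) and 0.04 (intervention):

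- As booked, control: 0.172 × (1 + 0.92 + 0.8464) = 0.476.
- As booked, intervention: 0.136 × (1 + 0.96 + 0.9216) = 0.392. Difference 0.084.
- Fixed, control: 3 − 0.9 × (0.92 + 0.8464 + 0.7787) = 0.709.
- Fixed, intervention: 3 − 0.9 × (0.96 + 0.9216 + 0.8847) = 0.510. Difference 0.199.
- Share kept: 0.084 / 0.199 = 42%. The control count is 33% lower than on the fixed schedule (0.476 / 0.709 = 0.67).

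With K = 6 and the same rates, the means are 0.846 vs 0.739 as booked and 1.926 vs 1.308 fixed, so about 17% is kept (0.107 / 0.618).

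These rates imply cumulative drop-out of 1 − 0.92³ = 22% vs 1 − 0.96³ = 12% over three visits, and 39% vs 22% over six. Both are above the planned 10%.

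**Illustration 2: total drop-out near the planned figure.** Drop-out is 10% control and 5% intervention in total, spread evenly over the visits, with a 10% miss chance per visit while in care. A patient who attends j visits' worth of follow-up and then disappears adds 0.1j misses under rule (a), 0.1j + 1 under (b), and 0.1j + (K − j) under (c).

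| Rule for appointments after drop-out | K = 3: control vs intervention | K = 6: control vs intervention |
|---|---|---|
| (a) none counted | 0.280 vs 0.290 | 0.565 vs 0.582 |
| (b) only the one at which the patient disappears | 0.380 vs 0.340 | 0.665 vs 0.632 |
| (c) all planned to month 6 | 0.480 vs 0.390 | 0.915 vs 0.757 |

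Rule (b) keeps 0.040 / 0.090 = 44% of the difference under (c) with three visits, and about 21% with six. Over a wider grid (K = 3 or 6, miss chance 10% or 20%, control drop-out 10% or 20%, intervention 5%), intervention minus control runs from +0.01 to +0.11 under (a), −0.02 to −0.12 under (b), and −0.08 to −0.47 under (c).

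**Does a denominator alone repair this?** Not reliably. Over the same grid, the mean proportion of counted appointments missed differs by 0.00 to +0.01 under (a), −0.02 to −0.08 under (b), and −0.02 to −0.09 under (c). Dividing by booked visits helps under (b) and does nothing useful under (a). Dividing by a number common to all patients only rescales the count. The repair comes from fixing which visits count.

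**The case against.** The strongest reply is that the attenuation rests on a rule the protocol never states. The sentence on paper appointments describes what controls receive. It does not say that no appointment exists once a patient is absent. The Lost-to-follow-up definition points the other way, because it speaks of scheduled visits missed over three months, which suggests that they remain scheduled. This stands: the direction is implied by one passage and questioned by another, and is settled by neither.

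A reader might infer more, namely that early drop-outs necessarily score well and that the better-retained arm is made to look worse. The documents do not support that. A reversed sign appears only under rule (a), where even the appointment at which the patient disappears goes uncounted. A Defaulter is defined by one missed appointment for any reason, so that visit would ordinarily count. Under rule (b) the better-retained arm still has fewer misses; the difference is just smaller.

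It can also be said that the labels already catch drop-outs, that the table under Data analysis lists only weight, CD4 and viral load as continuous outcomes, and that exact formulas belong in an SAP. The labels do protect the categorical form: a patient who missed a visit is not scored as regular. They do not protect the numeric form, which Primary Outcomes names explicitly. Since the protocol names an unscaled count, this is more than a detail left open. Finally, complete-case analysis would probably leave drop-outs out, but the plan requires intention-to-treat as well.

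**Conclusion.** The point holds for the numeric form of the second primary outcome. The protocol fixes a raw count with no denominator, no set number of visits and no rule for visits after a patient stops attending. If only booked appointments are counted, a difference due to retention is attenuated toward no effect. If all planned visits are counted, it is not. Size and direction therefore depend on booking practice.

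Under the assumed rates about 42% of the difference is kept with three visits and 17% with six. With total drop-out nearer the planned 10%, the shares are similar (44% and 21%) but the differences are small in absolute terms: 0.03 to 0.04 misses per patient as booked against 0.09 to 0.16 on a fixed schedule. None of these rates comes from the protocol, so the figures show the mechanism and are not a forecast. The change is worth making before analysis, but the finding does not establish a bias in a known direction.

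**What to change.** Under Primary Outcomes, define one set of countable scheduled visits to month 6 that applies to both arms. Months 1, 3 and 6 are the natural candidates, but the protocol names all three only for intervention-arm counselling, so the sponsor must confirm that they apply to controls. Count each such visit not attended as missed for every randomised patient, including visits after drop-out and whether or not an appointment slip was issued. Analyse misses over visits due, either as a binomial proportion or as a count with log(visits due) as offset. State that visits after death or transfer are not due, so that they leave the denominator. Replace the and/or choice between visits attended and times defaulted with this single definition.

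The cost is a change of wording. Attendance is already taken from medical records at every visit. The small downside is that extra bookings outside the common schedule do not enter this analysis; they can be reported separately.
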